## Abstract

**Introduction:**

Acute kidney injury (AKI) is associated with increased morbidity and mortality following cardiac surgery. Data focusing on the patterns of AKI following major gastrointestinal surgery could inform quality improvement projects and clinical trials, but there is a lack of reliable evidence. This multicentre study aims to determine the incidence and impact of AKI following major gastrointestinal and liver surgery.

**Methods and analysis:**

This prospective, collaborative, multicentre cohort study will include consecutive adults undergoing gastrointestinal resection, liver resection or reversal of ileostomy or colostomy. Open and laparoscopic procedures in elective and emergency patients will be included in the study. The primary end point will be the incidence of AKI within 7 days of surgery, identified using an adaptation of the National Algorithm for Detecting Acute Kidney Injury, which is based on the Kidney Disease Improving Global Outcomes (KDIGO) AKI guidelines. Secondary outcomes will include persistent renal dysfunction at discharge and 1 year postoperatively. The 30-day adverse event rate will be measured using the Clavien-Dindo scale. Data on factors that may predispose to the development of AKI will be collected to identify variables associated with AKI. Based on our previous collaborative studies, a minimum of 114 centres are expected to be recruited, contributing over 6500 patients in total.

**Ethics and dissemination:**

This study will be registered as clinical audit at each participating hospital. The protocol will be disseminated through local and national medical student networks in the UK and Ireland.

Strengths and limitations of this studyOutcomes After Kidney injury in Surgery (OAKS) will be the first prospective study of postoperative acute kidney injury (AKI) in gastrointestinal and liver patients in the UK and Ireland. It will be disseminated through a collaborative medical student network, enabling rapid data collection on many thousands of postoperative patients. The results will be generalisable across the UK and Ireland.Unlike some previous studies that arbitrarily defined AKI, OAKS will identify AKI based on an algorithm in widespread routine clinical use in England. While, there are limitations to its application to patients with chronic kidney disease, the algorithm is based on the internationally recognised Kidney Disease Improving Global Outcomes (KDIGO) AKI staging guidelines.Although data will only be collected on variables for which there is a known biologically plausible causative relationship with AKI, this observational study can only identify associations (not causation) between possible predisposing factors and AKI. OAKS will be hypothesis generating, identifying areas for further study. It will also generate the data required to design and power robust randomised clinical trials in the future.The snap-shot audit methodology limits the quantity and complexity of data it is feasible to collect. Fluid therapy and sepsis may be key factors related to AKI, but it would be difficult to collect robust data on these variables in a student-driven audit. Data on intraoperative contamination will be collected as a surrogate for postoperative abdominal and wound sepsis. Anastomotic leak will be recorded as this is a significant early septic complication.Not all patients will have blood test results available during the 1 year follow-up window. It is possible that some patients will have persistent renal dysfunction at 1 year, but blood tests will be unavailable to identify this. Therefore, rates of persistent renal dysfunction identified in this study are likely to be under-estimates.

## Background

Studies in cardiac surgery suggest that postoperative acute kidney injury (AKI) is common and strongly associated with increased morbidity, mortality and healthcare costs,^1–3^ but there is less evidence on the incidence and burden of AKI following gastrointestinal and liver surgery. Previous studies have reported the incidence of postoperative AKI after gastrointestinal surgery between 1 and 22%;^4–7^ this broad range reflects both heterogeneity in definitions of AKI and the limitations of retrospective data analysis.

### The need for further evidence

The National Confidential Enquiry into Patient Outcome and Death ‘Adding Insult to Injury’ report recommended that predictable and avoidable AKI should never occur.^8^ Moreover, National Health Service (NHS) England has recognised AKI as a key priority for improvement in its 2015–2016 Commissioning for Quality and Innovation framework.^9^ However, there are currently no reliable estimates of the incidence of postoperative AKI in gastrointestinal surgery, making it impossible to benchmark and audit local performance. A lack of clarity regarding potential factors associated with the development of postoperative AKI makes it difficult to consistently identify targets for interventions aimed at reducing its incidence.^5^
^7^
^10^ Reliable data on patterns of postoperative AKI could inform future quality improvement projects and clinical trials.

### Primary aim

The primary aim of the Outcomes After Kidney injury in Surgery (OAKS) study is to determine the incidence of postoperative AKI after major gastrointestinal and liver surgery.

### Secondary aims

The secondary aims of the OAKS study are to determine the short-term and mid-term morbidity and mortality associated with postoperative AKI and to identify perioperative variables that are associated with postoperative AKI.

## Methods

### Study design

A multicentre prospective cohort study disseminated through collaborative medical student networks (figure 1).

**Figure 1 BMJOPEN2015009812F1:**
[figure not shown]
STARSurg ‘Mini-Team” structure, roles and responsibilities.

### The STARSurg network

Student Audit and Research in Surgery (STARSurg) is the UK's national medical student research collaborative, run by the Surgical Research Gateway (SURG) Foundation (registered charity number 1 159 898). STARSurg is co-ordinated by a team of medical students and surgeons. The collaborative model and the educational benefits to participating students have previously been described elsewhere.^11^
^12^

### Study setting

Hospitals in the UK and the Republic of Ireland that offer elective or emergency gastrointestinal or liver surgery will be invited to participate. Each centre may contribute up to four, 2-week sets of consecutive patient data.

### Inclusion criteria

Adult patients (age ≥18 years) undergoing any gastrointestinal resection, liver resection or reversal of ileostomy or colostomy;Elective and emergency patients may be included;Open, laparoscopic, laparoscopic-assisted, laparoscopic-converted and robotic procedures may be included.

### Exclusion criteria

No baseline preoperative creatinine available;Previous kidney transplant;Renal replacement therapy (any form of dialysis) in the 90 days preceding operation;Appendicectomy;Transplant surgery;Gynaecological primary indication;Urological primary indication;Vascular primary indication.

### Patient identification and data collection

Operating lists and theatre computer systems will be screened daily to identify eligible patients. The preoperative and operative data fields will be completed at the earliest opportunity following surgery. Collaborators will actively follow-up patients in the postoperative period, completing 30-day and 1 year follow-up promptly.

### Primary outcome

The primary outcome measure will be the incidence of AKI within 7 days of the indexed operative procedure. This period of 7 days has been selected to only capture AKI directly attributable to insults sustained during the perioperative period.

Collaborators will submit raw creatinine values to the study database. AKI will be identified using an adaptation of the National Algorithm for Detecting Acute Kidney Injury classification system (figure 2), which is based on Kidney Disease Improving Global Outcomes (KDIGO) AKI guidelines.^13^ It was introduced by NHS England in June 2014 in a Patient Safety Alert requiring standardisation of the identification of AKI across the UK.^14^ If serum creatinine is not available over the past 7 days, the National Algorithm defines baseline creatinine as the median of all measured creatinine levels over the past year. It would not be practical for study collaborators to manually derive this value; therefore the algorithm has been adapted to require the most recent preoperative serum creatinine measurement. To identify emergency patients who had already developed AKI at admission, both the first creatinine measured on admission and the most recent preadmission creatinine will be required for emergency patients. A full description required creatinine data points is available in the online supplementary file (data points 11 and 29). In this observational study no extra blood tests will be performed, other than those ordered by the clinical team.

**Figure 2 BMJOPEN2015009812F2:**
[figure not shown]
Adaptation of the national algorithm for detecting acute kidney injury.^14^ RV, reference value; OAKS, Outcomes After Kidney injury in Surgery.

### Secondary outcomes

Secondary outcome measures will include:
Incidence of AKI within 48 h of surgeryPersistent renal dysfunction at dischargePersistent renal dysfunction at 12 monthsRegular renal replacement therapy (any form of dialysis) at 12 months30-day major complication rate (Clavien-Dindo grades III-V)30-day minor complication rate (Clavien-Dindo grades I-II)Mortality at 12 months

Persistent renal dysfunction will be defined as an increase from baseline of chronic kidney disease (CKD) stage, as defined by the Kidney Disease Outcomes Quality Initiative.^15^ In addition to serum creatinine, all other variables required to calculate estimated glomerular filtration rate (eGFR) using the Chronic Kidney Disease Epidemiology Collaboration formula will be collected.^16^ For the 30-day outcome, the single eGFR value nearest to postoperative day 30 will be used. For the 1 year outcome, blood tests taken 9–15 months postoperatively will be considered. Two separate eGFR values recorded at least 3 months apart will be required to demonstrate a persistent increase in CKD stage.

Complications will be recorded using the Clavien-Dindo classification, a standardised, internationally validated scoring system for postoperative complications.^17^ The highest grade complication (grade I-V) experienced by each patient will be recorded.

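### The early renal outcome is listed at discharge but defined by the eGFR nearest day 30 with no window, so a creatinine from the 7-day AKI window can also set the 'persistent' status

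*Protocol article*

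**What the plan says.** The abstract of the protocol article states: "Secondary outcomes will include persistent renal dysfunction at discharge and 1 year postoperatively". The list under Secondary outcomes also puts the early renal outcome at discharge and the late one at 12 months. The only 30-day entries in that list are the two Clavien-Dindo complication rates, which use no eGFR.

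The text below the list defines the condition: "Persistent renal dysfunction will be defined as an increase from baseline of chronic kidney disease (CKD) stage". It then gives the measurement rules:

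- Early: "For the 30-day outcome, the single eGFR value nearest to postoperative day 30 will be used".
- Late: "For the 1 year outcome, blood tests taken 9–15 months postoperatively will be considered".
- Confirmation: "Two separate eGFR values recorded at least 3 months apart will be required to demonstrate a persistent increase in CKD stage".

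No rule is given for a discharge value. For the primary outcome the article says: "The primary outcome measure will be the incidence of AKI within 7 days of the indexed operative procedure". The same section adds that no blood tests are taken beyond those the clinical team orders.

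**The concern.** Three things follow from reading these statements together.

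1. The listed outcome (discharge) has no measurement rule, and the rule that is given (day 30) belongs to no listed renal outcome. Two analysts could derive different variables from the same data.
2. The early rule has no limits, so it returns a value whenever any postoperative creatinine exists, however early.
3. AKI and early dysfunction are both judged from serum creatinine against baseline. If the value nearest day 30 comes from days 0–7, exposure and outcome can be the same measurement.

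The third point bears on the secondary aim of describing the morbidity associated with postoperative AKI. In patients whose value is reused, a creatinine that is still raised counts once as AKI and may count again as failure to recover. The apparent link between the two would be inflated and incomplete recovery overstated.

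**Working it through.** The article gives no figure for this point, so there is none to reproduce. The check compares the passages and then applies the rule as written.

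**Time points side by side**

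| Place in the protocol article | Early renal time point | Window |
|---|---|---|
| Abstract, Methods and analysis | Discharge | none |
| Secondary outcomes, list | Discharge | none |
| Secondary outcomes, definition | Day 30 | none |
| Secondary outcomes, definition (1 year, for comparison) | not applicable | 9–15 months |

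The two-value requirement cannot be met by a single day-30 value, so it has to be read as applying to the 1-year outcome. By the article's own standard, then, one early value does not demonstrate persistence.

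**When does an early value remain nearest to day 30?**

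Inputs: target day 30, and AKI window days 0–7 (Primary outcome). A creatinine on day d, with d ≤ 7, lies 30 − d days from the target. A later test on day t is strictly nearer only if |t − 30| < 30 − d, that is, if t falls on days d + 1 to 59 − d.

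| Day of early value (d) | Distance from day 30 | Replaced only by a test on days |
|---|---|---|
| 3 | 30 − 3 = 27 | 4 to 56 |
| 5 | 30 − 5 = 25 | 6 to 54 |
| 7 | 30 − 7 = 23 | 8 to 52 |

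A test on day 6 or 7 would replace a day-5 value but would itself lie inside the AKI window. To move the assessment out of that window, the patient needs a test after day 7 that is nearer to day 30. No such test is scheduled, and nothing in the article excludes a value from days 0–7.

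**How many patients?**

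The documents do not give the share of patients without a later test, so this is an illustration only. Inputs: 6840 patients (Anticipated minimum recruitment), AKI incidence 1–22% (the range from earlier studies in Background), and an assumed 10–50% of AKI patients with no later test nearer to day 30.

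- Low end: 6840 × 0.01 × 0.10 = 6.84, about 7 AKI patients.
- High end: 6840 × 0.22 × 0.50 = 752.4, about 752 AKI patients.

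These are AKI patients whose early status would rest on an AKI-window value. They are not the number counted as having dysfunction, because the CKD stage must also have risen. The range is too wide to size the problem. It shows only that the documents do not bound it.

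**The case against.** The strongest objection is that an article condenses a fuller protocol. The article refers to a supplementary file for the required creatinine data points, and a window may be stated there. This stands for the missing window, which is why that part is conditional. It does not remove the mismatch between discharge and day 30, since the article states both.

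It can also be said that the only specified multivariable model admits variables arising before the operation, so postoperative AKI is not a covariate in it, and that no stated analysis regresses early dysfunction on AKI. That is correct. However, the secondary aim of measuring morbidity associated with AKI calls for some comparison by AKI status, and this outcome is one of those named in the abstract.

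Several stronger readings are tempting but not supported:

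- **That two distinct outcomes share one label.** The list has one early renal outcome and the text has one early rule. One outcome worded inconsistently is the simpler reading.
- **That the value could come from months after surgery.** The rule sets no upper limit, but Patient identification and data collection says the 30-day follow-up is to be completed promptly, which makes very late values doubtful.
- **That a large share of patients is affected, mostly with values from days 0–7.** The article gives neither lengths of stay nor post-discharge testing rates.
- **That AKI makes the early outcome positive by definition.** The criteria differ. AKI that has recovered by the last test, or that does not change the CKD stage, is not counted. An inpatient value taken after day 7 lies outside the AKI window altogether.

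**Conclusion.** The discharge versus day-30 mismatch is a plain inconsistency in the article and needs correcting whatever the supplement contains. The overlap with the AKI window is a consequence of the rule as written. It affects only patients with no test after day 7 that is nearer to day 30, and for them any association between AKI and early dysfunction is partly built in.

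This conclusion assumes that the rule is applied literally and that no window is set elsewhere. The affected share is unknown. Severity is moderate: one secondary outcome is involved. The primary outcome does not use the rule, and the 12-month renal outcome has its own window and a two-value requirement.

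**What to change.** Make the abstract, the outcome list and the definition name one early time point.

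- **If it is day 30:** use the eGFR nearest day 30 within a stated window that starts after day 7. Treat patients with no value in that window as missing, and do not fill the gap from days 0–7.
- **If a discharge value is also reported:** define it as the last creatinine before discharge, keep it separate, and do not call it persistent. Do not use values from days 0–7 to estimate the association with AKI. Relabelling alone is not enough, because a discharge value taken by day 7 has the same overlap.

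If the supplementary file already sets such a window, state it in the article.

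The change needs only wording and one derivation rule. The cost is that fewer patients will have a valid 30-day value, so the number missing should be reported by AKI status.

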### Factors associated with AKI

A key aim of OAKS is to identify perioperative factors that may be associated with subsequent development of AKI. To record this, data will be collected on patient-related, disease-related and pharmaceutical variables (table 1). Detailed description of all data fields is available in the online supplementary file.

**Table 1 BMJOPEN2015009812TB1:** Explanatory data variables collected for OAKS Study

Patient	Disease	Pharmaceutical
Age	Urgency of operation	Perioperative use of NSAIDs
Gender	Underlying pathology	Perioperative use of ACEi or ARBs
Ethnicity	Intraoperative contamination	Perioperative use of diuretics
American Society of Anaesthesiologists (ASA) Score	Baseline haemoglobin and albumin	Postoperative aminoglycosides
History of ischaemic heart disease	Perioperative red cell transfusion	Perioperative use of intravenous contrast
History of congestive heart disease		
History of cerebrovascular disease		
History of hypertension		
History of diabetes		
Smoking status		

ACEi, ACE inhibitors; ARB,angiotensin-receptor blocker; NSAIDs,non-steroidal anti-inflammatory drugs; OAKS, Outcomes After Kidney injury in Surgery.

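### Keeping only the highest Clavien-Dindo grade turns the minor complication rate into a worst-grade rate, and the article does not say whether AKI itself counts towards that grade

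*Protocol article*

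**What the plan says.** The Secondary outcomes section lists a 30-day major rate for grades III-V and, separately, a "30-day minor complication rate (Clavien-Dindo grades I-II"). It describes the scale as "a standardised, internationally validated scoring system for postoperative complications" and fixes what is collected: "The highest grade complication (grade I-V) experienced by each patient will be recorded".

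The Secondary aims give these outcomes their purpose, which is to "determine the short-term and mid-term morbidity and mortality associated with postoperative AKI". They will therefore be compared between patients with and without AKI.

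The primary outcome is the "incidence of AKI within 7 days of the indexed operative procedure", so the AKI window lies inside the 30-day complication window. AKI is derived separately from the grade: "Collaborators will submit raw creatinine values to the study database". One other complication has its own item, according to the strengths and limitations list: "Anastomotic leak will be recorded as this is a significant early septic complication". Field definitions are left to a supplement that is not shown: "Detailed description of all data fields is available in the online supplementary file".

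**The concern.** Two features of the single highest grade affect the AKI-morbidity comparison.

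- **The minor rate.** A patient with both a minor and a major complication leaves the grade I-II numerator but stays in the denominator. If AKI patients have more major complications, more of their minor events are hidden. The minor rate can then look lower with AKI even when the risk of a minor event is the same in both groups.
- **AKI inside its own outcome.** Postoperative AKI falls within the plain scope of a scale for postoperative complications, and nothing in the article takes it out. If a collaborator grades the AKI itself, exposure and outcome are partly the same event. A bare grade does not show which event produced it, so this could not be undone at analysis.

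The short-term burden of AKI is a stated aim, and the Discussion says the results will define targets for quality improvement and future trials. The 12-month mortality and dialysis outcomes do not use the grade and are unaffected.

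**Working it through.** The article gives no complication rates and no figure to reproduce. All complication rates below are assumptions. From the article come the highest-grade rule, the anticipated 6840 patients, the 1% to 22% range of earlier AKI incidence, and two-sided p<0.05.

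**1. What the minor rate measures.** With only the highest grade kept:

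recorded minor rate = P(any I-II event and no III-V event) = P(minor) − P(minor and major).

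The overlap term decides the size. With an assumed 30% of patients having any minor event:

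| Major rate | No overlap | Independent | Every major patient also has a minor event |
|---|---|---|---|
| 10% | 30% | 0.30 × 0.90 = 27% | 30 − 10 = 20% |
| 20% | 30% | 0.30 × 0.80 = 24% | 30 − 20 = 10% |
| 30% | 30% | 0.30 × 0.70 = 21% | 30 − 30 = 0% |

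**2. Effect on a comparison by AKI status.** Assume a 50% minor risk in both groups (true OR 1), independence within each group, and major rates of 40% with AKI and 10% without.

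- With AKI: 0.50 × (1 − 0.40) = 0.30. Without: 0.50 × (1 − 0.10) = 0.45.
- OR = (0.30/0.70) / (0.45/0.55) = 0.52.
- With major rates of 30% and 10%: 0.35 and 0.45, OR = (0.35/0.65) / (0.45/0.55) = 0.66.
- With no overlap: 0.50 in both groups, OR 1.

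The two recorded categories are mutually exclusive, so any complication (I-V) is their sum: 0.30 + 0.40 = 70% with AKI and 0.45 + 0.10 = 55% without. No patient with a complication drops out of that numerator.

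**3. Effect if AKI is graded.** Assume AKI has no true effect on other complications. Let the background rate of any complication be b = 35% (minor 23%, major 12%). Let s be the share of AKI patients with no other complication whose AKI is graded, as minor.

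- Any complication given AKI = b + (1 − b)s.
- Minor rate given AKI = 0.23 + 0.65s.

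| s | Any, AKI v no AKI | OR | Minor, AKI v no AKI | OR |
|---|---|---|---|---|
| 0 | 35% v 35% | 1 | 23% v 23% | 1 |
| 0.25 | 51% v 35% | 1.95 | 39% v 23% | 2.16 |
| 0.50 | 68% v 35% | 3.86 | 56% v 23% | 4.18 |
| 1 | 100% v 35% | infinite | 88% v 23% | 24.6 |

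With 6840 patients and s = 0.25, a two-sided 5% comparison of any complication would declare this artefact significant with probability 0.79 at 1% AKI incidence (about 68 AKI patients) and above 0.999 at an assumed 10% (684 AKI patients).

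**4. Whether it could be removed later.** The creatinine data show who had AKI, not whether AKI produced the grade. The anastomotic leak item identifies only one other possible cause. From what the article describes, the grade cannot be separated afterwards.

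**The case against.** The strongest reply is that the second part rests on silence. The article does not say that AKI is graded. Which events count is data-dictionary content, which an article commonly leaves to its supplement, and collaborators must also complete e-learning on the classification. A reader might infer that AKI is counted, or that every AKI patient is complication-positive by definition. The article supports neither: AKI comes from creatinine values through an algorithm, and an AKI so defined need not be entered as a complication. This stands, and the circularity is therefore stated only as a condition.

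On the first part, a reader might infer that the minor rate falls whenever major complications rise. That is wrong without overlap, as the no-overlap column shows. The odds ratios rest on assumed rates and on independence. The highest-grade rule is also printed in the same section as the two rates, so a careful reader can see what I-II means, and nothing needed for an any-complication or ordinal analysis is lost. This too stands, but it shows that the remedy is free, not that the listed minor rate is safe to compare by AKI status.

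The two mechanisms push the minor rate in opposite directions, so its net bias is unknown. Finally, the article speaks of morbidity associated with AKI and disclaims causation, so it should not be read as attributing complications to AKI.

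**Conclusion.** The point holds in a limited form.

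- **Minor rate.** This follows from what the article states. The listed rate is the proportion whose worst event is grade I-II, and comparing it by AKI status can mislead when patients have both minor and major events. The size depends on overlap and on the difference in major rates: nothing without overlap, and an OR of 0.52 instead of 1 under the assumed 50% minor risk, independence, and 40% v 10% major rates.
- **Circularity.** This is conditional. It is zero if AKI is never graded. If AKI is graded in a quarter of AKI patients with no other complication, the OR for any complication is 1.95 with no true effect, under the assumed 35% background. The article does not settle which case applies, and a grade without its cause could not be corrected later.

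The point concerns the 30-day complication outcomes only. The primary outcome is untouched.

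**What to change.** - For comparisons by AKI status, report any complication (I-V) alongside major (III-V), or analyse grade 0 to V as one ordinal outcome. Label the I-II category 'worst grade I-II' wherever it is reported. This uses the same field and costs nothing.
- State whether AKI counts towards the grade. If the data dictionary already excludes it, a sentence saying so is enough.
- If it does not, add one tick box, 'highest-grade event is AKI', before data collection starts, and repeat the AKI-morbidity comparison without those AKI-driven grades. The dictionary should say how to tick the box when another event reaches the same grade. The box does not recover a lower-grade complication in the same patient. Resetting those patients to no complication may therefore understate other morbidity, and the comparison with and without the reset should be shown together.

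The cost is one extra field and some attribution judgement by student collaborators, which is not trivial in patients with several complications.
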